^29^ It may appear logical that decisions about initiating cholesterol-lowering medication should be based on the patient's cholesterol level, and indeed this was the preferred approach in the pre-CVD risk era.^30^
^31^ However, this approach would not necessarily result in the greatest benefits and is not justifiable based on the available evidence. Despite this, there is evidence that this approach prevails in some areas. After adjusting for other CVD risk factors, lipid profile has been found to predict statin initiation in a US study^32^ and a randomised theoretical experiment in Australia highlighted clinicians’ preferences for managing individual risk factors over absolute risk.^33^ To further compound the problem, patients find it difficult to make decisions based on future risks and tend to preferentially focus on cholesterol levels when considering taking statins.^34^
^35^

In 2014, guidelines for England and Wales on lipid modification reduced the predicted risk threshold at which patients should be offered statins from a 20% 10-year risk to 10%.^5^
^7^ This recommendation was met with considerable concern from the medical community that it would lead to widespread overprescribing of statins with little clinical benefit but considerable potential for harm.^36^
^37^ This widely publicised criticism may have increased concerns that risk scoring leads to oversimplification of clinical decisions and overprescribing and may have, perversely, decreased the use of risk scoring and reinforced the use of lipid levels to guide decision-making. There is some evidence to suggest there was a decrease in statin initiations around this time due to the negative media attention.^38^

This research will investigate the relationship between lipid profile, QRISK2 score and subsequent initiation of statins by primary care clinicians. This will give an indication of the patient factors that are influencing the decisions clinicians make in routine practice when considering the use of statins and how this has changed in response to external factors.

The consistent use of risk scoring can result in more targeted prescribing and fewer patients being prescribed medication overall^39^ which maximises the efficiency and cost-effectiveness of treatment at a population level.

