Immunosuppressant medication	Yes, no
Year quartile	1st, 2nd, 3rd, 4th

*Schizophrenia, bipolar affective disorder, mania or psychosis (unspecified), psychotic depression.

†Systemic lupus erythematosus, scleroderma, Bechet's syndrome, other inflammatory arthritis.

BMI, body mass index; BP, blood pressure; CVD, cardiovascular disease; HDL, high-density lipoprotein.

The potential cohort size can be estimated from the literature. Feasibility data from the THIN database identified over 360 000 patients over 2 years who were eligible for statin treatment for the primary prevention of CVD and had a lipid result and blood pressure coded on their medical record.^22^ Over a 5-year period we should expect to identify over double this number. Another cohort identified just over two million patients in the THIN database in the age range where NHS health checks are offered.^48^ Given that every patient who attends an NHS health check should have a lipid test undertaken and 20% of 40–75 years old are invited to have a health check each year, with ∼50% taking up this offer.^49^ This would generate around 200 000 coded lipid results in the target population annually.

The accuracy of the post hoc QRISK2 calculations will be tested through comparisons with corresponding coded QRISK2 scores in patients where these are available.

Additional modelling will also be undertaken to consider whether having a QRISK2 score coded on the medical record affects the probability of having a statin prescribed after adjustment for the level of CVD risk. Secondary analysis will also establish whether the threshold for initiating statins has changed over the course of the study period. The mean lipid levels and QRISK2 scores (both coded and calculated post hoc) of those initiated on statins and those not initiated on statins will be calculated each year to reveal any trends in the thresholds for initiation.

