Finally, prescriber-level data will be analysed to establish whether individuals tend to be influenced more by lipid levels or risk score when initiating stains and whether this behaviour is consistent over time. A score that illustrates the propensity to prescribe based on lipid levels will be calculated for individual clinicians. This will be generated by comparing the number of statin initiations to patients with a total cholesterol of ≥6.5 mmol/L with the number of statin initiations to patients with a total cholesterol of <6.5 mmol/L. Only clinicians who initiated 10 or more statin prescriptions over the study period will be analysed as scores for clinicians with fewer initiations may not be representative of their behaviour. The distribution of these scores will be described. For clinicians who initiated statins in every year of the study, their score will be calculated for the 2-year periods 2012–2013 and 2015–2016. The scores for each period will be split into quintiles. The tendency for clinicians to stay in the same quintile, or move quintile, will then be described.

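### Quintiles cut separately in each period record only a clinician's rank, so the movement table cannot tell no change from a change shared by all clinicians

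*Protocol article*

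**What the plan says.** The last paragraph of the Analysis section of the protocol article sets out the prescriber-level work. It is to show whether individual clinicians respond more to lipids or to risk score, and "whether this behaviour is consistent over time".

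- **Score.** It is formed by "comparing the number of statin initiations to patients with a total cholesterol of ≥6.5 mmol/L with the number of statin initiations" below that level.
- **Who is included.** "Only clinicians who initiated 10 or more statin prescriptions over the study period will be analysed". The two-period step is limited further, to clinicians who initiated statins in every study year.
- **Periods.** For these clinicians "their score will be calculated for the 2-year periods 2012–2013 and 2015–2016".
- **Yardstick.** "The scores for each period will be split into quintiles".
- **Summary.** "The tendency for clinicians to stay in the same quintile, or move quintile, will then be described".

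The article states no cut-points common to the two periods and plans no comparison of the scores themselves between periods. The score distribution that it does promise comes before the two-period step and concerns the whole-study scores.

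**The concern.** A quintile formed inside one period gives a clinician's place among colleagues in that period. It says nothing about the level of the score. About 20% of clinicians fall in each quintile in both periods, wherever the scores lie. If all clinicians became less lipid-led, or all more so, by an amount that kept their order, the movement table would match that of a group in which nobody changed.

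This matters because the question posed is about the consistency of behaviour, and the periods lie either side of 2014. The Introduction says that the risk threshold for offering statins was lowered from 20% to 10% in that year, and that the public criticism which followed may have pushed clinicians back towards lipid levels. A change affecting many clinicians together is therefore a possibility that the protocol itself raises. Quintile agreement could then be taken as consistent behaviour when it shows only consistent rank.

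**Working it through.** **No plan figure to reproduce.** The article attaches no number to this analysis. Its sample-size figure (10 per degree of freedom × 57 = 570) concerns the regression model and plays no part here.

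**Step 1: the exact argument.** Let a clinician have *a* initiations at total cholesterol ≥6.5 mmol/L and *b* below it. The score may be the ratio s = a/b or the share a/(a+b) = s/(1+s). The share rises with s, so both give the same quintiles. Suppose every score changes by one common increasing function, for example s₂ = k·s₁ with k = 0.5. The order of the s₂ is then the order of the s₁, and the period-2 cut-points move with the scores. Every clinician stays in the same quintile, for any k > 0. This needs no outside figure, but it describes true scores without sampling error.

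**Step 2: volume.** The minimum of 10 initiations applies to all five years. Spread evenly, it gives 10 ÷ 5 × 2 = 4 initiations per two-year period, so chance movement has to be allowed for.

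**Step 3: simulation.** All of these inputs are assumptions, as the article gives none of them:

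- 20,000 clinicians, with log-odds that an initiation is at ≥6.5 mmol/L drawn as Normal(0, SD 0.6)
- a shared shift of 0, −0.5 or −1.0 log-odds between periods, taking the mean share from 0.50 to 0.50, 0.39 or 0.28
- binomial counts with equal volume per clinician, and ties broken at random

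Without sampling error, within-period quintiles give 100% staying at all three shifts. With the 2012–2013 cut-points kept for both periods, the −0.5 shift gives 24.7% staying and 75.3% moving down; the −1.0 shift gives 20.6% and 79.4%.

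With sampling error (percent same / down / up):

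| Initiations per period | Shift | Within-period quintiles | 2012–2013 cut-points |
|---|---|---|---|
| 4 | 0 | 24.5 / 37.9 / 37.5 | 24.6 / 38.1 / 37.4 |
| 4 | −1.0 | 24.0 / 37.9 / 38.1 | 23.5 / 59.2 / 17.2 |
| 10 | 0 | 30.6 / 34.5 / 34.9 | 30.5 / 34.0 / 35.4 |
| 10 | −1.0 | 28.9 / 35.1 / 36.0 | 25.0 / 67.8 / 7.2 |
| 20 | 0 | 36.5 / 31.9 / 31.5 | 36.5 / 32.3 / 31.2 |
| 20 | −0.5 | 35.8 / 32.1 / 32.1 | 32.3 / 56.3 / 11.4 |
| 20 | −1.0 | 35.1 / 32.3 / 32.6 | 24.7 / 72.7 / 2.6 |
| 50 | 0 | 47.6 / 26.2 / 26.2 | 47.6 / 26.5 / 25.9 |
| 50 | −1.0 | 45.5 / 27.0 / 27.5 | 22.1 / 77.8 / 0.2 |
| 200 | 0 | 66.1 / 16.9 / 17.0 | 66.1 / 16.8 / 17.0 |
| 200 | −1.0 | 64.3 / 17.8 / 17.9 | 20.7 / 79.3 / 0.0 |

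**Step 4: reading the table.** In the planned (within-period) table, the largest shift changes the share staying by at most 47.6 − 45.5 = 2.1 percentage points, and moves up and down stay balanced. With common cut-points the same shift produces a clear excess of downward moves at every volume.

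**The case against.** Several counter-arguments carry weight.

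- **Rank is a legitimate target.** The prescriber work serves the fourth objective, on variation between prescribers. Whether a clinician stays comparatively lipid-led among peers is a fair question, and period-specific quintiles answer it. This stands as a reason to keep them. It does not make rank the same thing as consistency of behaviour, and the text does not say that only rank is meant.
- **A shared shift may show elsewhere.** The Analysis section also plans yearly figures: "The mean lipid levels and QRISK2 scores (both coded and calculated post hoc) of those initiated on statins", with the same for those not initiated. These may reveal an overall trend. They are patient-level means, though, and cannot show whether individual clinicians changed.
- **Real tables will not show near-complete agreement.** This is right: at modest volumes chance moves most clinicians. The fault is insensitivity to a shared change, not false evidence of stability.
- **A shared shift is not established.** The Introduction describes influences pulling in opposite directions, and clinicians may have responded differently. Re-ranking of that kind is what the planned table can pick up.
- **Fixed cut-points have a drawback.** The score compares counts of initiations, so calendar changes in who is tested or eligible would also move clinicians across fixed cut-points. This stands, and is why such a table is offered only as an addition.

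The quintile sentence could also be read as meaning cut-points pooled over both periods. Nothing in the text says so.

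**Conclusion.** The point holds within the prescriber-level analysis. On the plain reading, the movement table cannot separate an absence of change from a change shared by all clinicians. The mechanism is exact for true scores. Under the simulated assumptions on spread, shift, volume and ties, the table also looks nearly the same with and without a shared shift once sampling error is added (a difference of at most 2.1 points in the share staying).

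A reader might infer more, and the documents do not support it:

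- **That the study's aim of detecting change over time fails.** The aim is worded for patients, not prescribers, and the yearly means bear on it.
- **That the protocol will report unchanged behaviour.** It says only that the tendency to stay or move will be described.
- **That every clinician would be seen to stay put.** This is true only without sampling error.
- **That a common shift is the likeliest outcome.** The Introduction makes it possible, not most probable.

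The analysis is secondary and descriptive, so this is a modest correction. It is worth making because the analysis as fixed does not fully answer the question that it poses.

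**What to change.** 1. Beside the quintile table, report the distribution of scores in each period and the distribution of each clinician's change in score (median and spread). The median change shows a shared shift. The spread will include chance variation where initiations are few, and this should be said. If the score is kept as a ratio, take the change on the share scale, because a ratio has no value for a clinician with no initiations below 6.5 mmol/L in a period.
2. State that quintiles are formed within each period, and label the movement table as stability of relative rank.
3. Optionally, add a second movement table that applies the 2012–2013 cut-points to both periods, with a note that changes in who is tested or eligible can also shift scores.

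Cost: a change of wording, one extra table and, if the third step is taken, a second table with its caveat. The period scores are already to be calculated, so no new data are needed.

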## Potential limitations

The use of electronic patient records, while excellent for allowing access to large quantities of real-life data, does not allow complete understanding of the decision-making process. We will not be able to explore why a patient with a particular lipid profile does or does not receive a prescription for a statin. We cannot gain insight into what discussion took place as to the risk and benefits of treatment or even whether the clinician discussed the lipid result and CVD risk with the patient. It is also difficult to know to what extent clinicians are using QRISK2 scores in their decision-making process because, as only coded data are available, QRISK2 score may be calculated but not recorded in GP records. The Vision patient record system automatically displays a CVD risk score for patients who may benefit from CVD risk reduction^46^ and the clinician could act on this information without it being coded. This would result in patients being prescribed a statin based on their CVD risk without this being apparent through the coded information.

It is also possible that some patients will have their lipid levels checked outside of the primary care system (either in secondary care or the private sector) and may be started on statins by their GP without the lipid levels being recorded in primary care. These patients would not be included in this cohort. However, it is unlikely that this will represent a significant proportion of patients initiated on statins. Similarly, a small proportion of patients may be initiated on statins by secondary care or private clinicians and the prescription continued by their GP. In this scenario, the GP may not be involved in the decision-making process but this would not be identified from the data. Again, this is likely to be a very small proportion of the total statin initiations in the UK and is not of central interest as the decision to prescribe was made outside the primary care setting and is, therefore, unlikely to affect the validity of our conclusions.

In conclusion, while the methodology will not facilitate complete understanding of the individual decision-making consultations, it will provide new and valuable insight into the way that lipid levels and cardiovascular risk are currently being used in primary care to inform the decision to prescribe or offer statins. We will be able to establish whether the use of risk scoring is resulting in more evidence-based prescribing and improve understanding of some of the factors affecting decision-making which may inform future policy and clinical guidance.

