## Aims and objectives

*Aim*: To establish whether UK primary care patients are initiated on statins based more on their lipid levels or on their predicted CVD risk and if this has changed over time.

*Objectives*:

For primary prevention of CVD
To evaluate how lipid levels and CVD risk independently predict subsequent prescribing of statins.To determine if the relationship between lipid levels, QRISK2 score and statin prescribing has changed following recent guideline changes.To investigate the contribution that calculating a QRISK2 score has on the probability of initiating statin therapy.To investigate interprescriber variation when initiating statins.

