### Predictor variables

Sociodemographic details will be obtained for each patient: age, sex, ethnicity, Townsend quintile and rurality indicator (see online supplementary appendix III). General practice and clinician ID will also be recorded.

10.1136/bmjopen-2016-013120.supp3supplementary appendix III

Patient variables will include the cardiovascular risk factors required to calculate QRISK2; age, sex, ethnicity, postcode, smoking status, diabetes status, family history of CVD, CKD (stage 4 or 5), atrial fibrillation, hypertension treatment, rheumatoid arthritis, lipids, blood pressure and body mass index (BMI). Other clinical data that may affect the decision to prescribe statins will also be collected comprising of; liver transaminase levels, systemic inflammatory conditions, severe mental health conditions and HIV.

Data on medication prescriptions will be extracted. Patients who received a prescription for antihypertensive medication up to 180 days prior to the index date will be considered to have been on treatment for hypertension. Prescriptions of antipsychotics, corticosteroids and immunosuppressant medication will be recorded as these may change the threshold for prescribing lipid-lowering medication.

All included patients will have a QRISK2 score calculated post hoc from the available data. In addition, any coded QRISK2 score prior to and including the follow-up period will be extracted.

The date when predictor variable data are collected will vary depending on whether or not the patient has a QRISK2 score coded during the follow-up period. For patients with a coded QRISK2 score on the index date or in the follow-up period, the date of QRISK2 recording will be used as the date for collecting data on predictor variables and the most recent data (including the date of QRISK2 coding) will be recorded. If more than one QRISK2 score is coded in the follow-up period, the latest date will be used for data collection to account for any variables that were updated during the follow-up period. For patients who do not have a coded QRISK2 score, the included data will be the most recent recorded before and including the end of the 60-day follow-up period.

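### The closing claim that the study can establish whether risk scoring makes prescribing more evidence-based goes beyond the analysis assigned to scoring, which looks only at whether a coded score changes the probability of a statin

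*Protocol article*

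**What the plan says.** Four parts of the protocol article bear on this.

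- **Aims and objectives.** The third objective is "To investigate the contribution that calculating a QRISK2 score has on the probability of initiating statin therapy".
- **Analysis.** The modelling that serves it asks if "having a QRISK2 score coded on the medical record affects the probability of having a statin prescribed after adjustment for the level of CVD risk". No interaction of coding with risk or with cholesterol is mentioned. Separately, Table 1 lists coded QRISK2 in five levels (four risk bands and missing) beside calculated QRISK2 for the primary model.
- **Predictor variables.** On timing, "any coded QRISK2 score prior to and including the follow-up period will be extracted". The follow-up period is also the 60-day window in which the outcome is counted.
- **Potential limitations.** The section says "It is also difficult to know to what extent clinicians are using QRISK2 scores in their decision-making process", since a "QRISK2 score may be calculated but not recorded in GP records". It adds that the record system displays a risk score automatically and that "the clinician could act on this information without it being coded". Its concluding paragraph then states: "We will be able to establish whether the use of risk scoring is resulting in more evidence-based prescribing".

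**The concern.** The closing sentence asserts three things: that use of scoring is observed, that scoring produces the change, and that prescribing becomes better matched to the evidence. The Introduction gives the last of these a meaning. It treats predicted risk as the best guide to benefit from statins and regards starting them on cholesterol level as unjustified by the evidence. More evidence-based prescribing would therefore show as a steeper gradient of initiation with risk and a flatter gradient with cholesterol among scored patients. The analysis assigned to scoring estimates neither gradient by coding status.

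At stake is what can be concluded. A raised odds ratio for coding could be taken as better prescribing when it reflects more prescribing at every level of risk. An odds ratio near 1 could hide a real shift towards high-risk patients. The article expects its findings to inform policy and guidance.

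**Working it through.** The article gives no figure on this point. Its one minimum sample, 10 × 57 = 570, follows from its inputs but does not bear on the claim. The check is whether the adjusted odds ratio (OR) for coding identifies targeting. All inputs below are assumptions.

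**1. Level against targeting, first set of inputs.** Shares of patients by calculated QRISK2 band (<10, 10–14.9, 15–19.9, ≥20%): 60/16/9/15%. Initiation without a code: 2/4/6/8%. Coded: 30% in each band. Coded initiation p1 follows from odds(p1) = OR × odds(p0). The adjusted OR is Mantel–Haenszel, Σ(ad/n) ÷ Σ(bc/n), over the four bands.

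- Uncoded: share of initiations at <10% risk = 0.60×0.02 ÷ (0.0120+0.0064+0.0054+0.0120) = 0.0120/0.0358 = 33.5%.
- OR 2 in every band: p1 = 3.92/7.69/11.32/14.81%. Adjusted OR = 2.00. Share at <10% = 0.0235/0.0682 = 34.5%, so targeting is unchanged.
- Band ORs 0.5, 1, 1.3, 1.5: p1 = 1.01/4.00/7.66/11.54%. Adjusted OR = 0.00724/0.00706 = 1.03. Share at <10% = 0.00606/0.03666 = 16.5%, about half.

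**2. Second set of inputs.** Shares 60/15/10/15%, uncoded initiation 2/6/9/12%, 30% coded, and a logistic model with band and coded (yes/no). The share of initiations at QRISK2 ≥10% in uncoded patients is 0.036/0.048 = 75%.

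| Pattern | Band ORs for coding | Adjusted OR | Share at ≥10%, coded |
|---|---|---|---|
| Uniform rise | 1.5 throughout | 1.50 | 74% |
| Better targeting | 0.5, 1.5, 1.8, 2.2 | 1.50 | 91% |
| Worse targeting | 2.6, 1.5, 1.2, 1.0 | 1.56 | 58% |
| Better targeting, little net change | 0.4, 1.0, 1.2, 1.4 | 1.01 | 90% |

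One value of the OR fits three opposite patterns, and a value near 1 fits clearly better targeting. Other inputs would change the sizes but would not make a single OR identify targeting.

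**3. Coding as a marker of use.** Suppose every coded patient was managed with a score, and so was a fraction u of uncoded patients. With risk p without a score and q with one, the uncoded risk is u·q + (1−u)·p. For p = 5% and true OR 3: odds = 3 × 0.0526 = 0.158, so q = 13.6%. At u = 25% the uncoded risk is 0.25×13.64 + 0.75×5 = 7.16%, and the OR seen is 0.158/0.0771 = 2.05. For u = 10, 25, 50 and 75% the OR seen is about 2.5, 2.0, 1.5 and 1.2 (almost the same at p = 2%). A true OR of 2 at p = 5% becomes 1.61, 1.34 and 1.15 at u = 25, 50 and 75%. The article gives no value for u.

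**4. Order.** Scores coded anywhere in the 60 days are extracted, and no rule stated in the article requires the code to precede the prescription. A score entered after the decision could therefore count as exposure.

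**The case against.** The strongest reply has four parts.

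- **Objective 3 promises nothing about quality.** This stands. The objective speaks only of the probability of initiation, and its analysis models that. A reader might infer that it promises better targeting, but its wording does not support that. Its one mismatch is calculating a score versus having one coded.
- **Table 1 can already show targeting.** This stands in part. Under the second set of inputs, with the coded band set equal to the calculated band, contrasts of each coded band with missing recover the band ORs and so separate better, uniform and worse targeting. It would be too strong to say that the planned data cannot describe targeting by risk. But the article does not designate those contrasts for this question, and no contrast of coding with cholesterol is planned. The yearly means of lipids and QRISK2 compare initiated with non-initiated patients and are not described as split by coding.
- **Model form belongs in a fuller document.** It is fair that a condensed article need not list interaction terms, and reading the scoring analysis as a single adjusted effect is an inference, though the natural one. The point does not rest on an omission. It rests on a stated claim that outruns both the stated question and the stated limitation.
- **Uncoded use is disclosed, and it only dilutes.** Disclosure stands, and in the calculation the OR moves towards 1 without reversing. But the disclosure makes the later sentence harder to sustain. The caveat that opens the concluding paragraph concerns individual consultations and does not limit the claim about scoring.

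**Conclusion.** The closing claim is not supported by the analysis assigned to scoring. That analysis can show whether patients with a coded score are more likely to receive a statin at a given risk. Without a designated contrast it does not show whether prescribing is better targeted. Because uncoded scores can be acted on and codes may follow the prescription, it does not show that use of a score brought the pattern about.

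The size is illustrative only: an OR of about 1.5 with 58% to 91% of coded initiations at or above 10% risk, and a true OR of 3 seen as anything from about 2.5 to 1.2. Band shares, initiation rates, coded proportion and extent of uncoded use are all assumed.

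A reader might go further and infer that a positive OR will be reported as proof of better prescribing. The article does not say so; it ties that analysis to the probability of a prescription. The primary analysis and the minimum sample are unaffected.

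**What to change.** 1. In the secondary coded-score model, prespecify coded (yes/no) × calculated QRISK2 band and coded × total cholesterol terms. Report the risk and cholesterol gradients separately for coded and uncoded lipid tests.
2. For this analysis, count a score as coded only if its date is on or before the date of the statin prescription.
3. Restate objective 3 and the closing sentence as the association between a coded QRISK2 score and statin initiation and its targeting. Do not describe it as an effect of calculating or using a score.

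Cost: two interaction terms and a date rule on data already to be extracted, a little more reporting, and a more modest claim.
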